### Secondary outcome measures

Several clinical assessments of UL function post-stroke will be exploited to evaluate participants’ UL performance before (baseline) and after training (post-day 1 and post-day 30). The motor section of Fugl-Meyer Assessment for Upper Extremity (FMA-UE) will be used to measure movement ability across the domains of reflex, movement, and coordination [33]. Participants’ functional ability will also be assessed using the streamlined Wolf Motor Function Test (WMFT) which includes six timed tasks: hand to table (front), hand to box (front), lift can, lift pencil, fold towel, and reach and retrieve [34]. The EmNSA will be employed to evaluate UL sensation (exteroception) through a wide range of subscales that include light touch, tactile discrimination, and proprioception [35]. Herein the effect of multiple training sessions on other somatosensory modalities such as tactile sensation and sharp-blunt discrimination will be examined. Additionally, both modified Ashworth scale (MAS) of spasticity [36] and visual analogue scale (VAS) [37] will be performed to monitor upper limb spasticity and pain intensity in participants, respectively. Note that the Star Cancellation Test [38] will merely be conducted at baseline to identify the presence of unilateral neglect in participants.

### Short study questionnaire

A short, hardcopy questionnaire that consists of seven Likert scale questions will be administered at the end of the last training. The purpose of this questionnaire is to obtain individual opinions on the robotic-based training from the participants. This questionnaire will be completed by both groups of participants based on their experience of participating in the proposed training. In the questionnaire, participants will be asked to express their agreement or disagreement with various statements, e.g. ‘I feel the long-term benefits of this therapy’ and ‘I feel satisfied when I got reward feedback during the session’, using a 7-point scale ranging from strongly disagree to strongly agree.

### Statistical analysis

All statistical analyses will be carried out using SPSS (ver. 28.0). Information obtained from the primary and secondary assessments will be recorded as text files. From the motor test data, different kinematic parameters will be computed: endpoint error and smoothness. Likewise, kinaesthetic performance will be estimated by the difference between the reference trajectory produced by the robot and the reproduced trajectory by the participants. Behavioural outcomes obtained from every training session will be computed to identify the improvements in kinematic parameters session by session: total number of successful outcomes and average endpoint error in reaching trajectories. Due to its superiority in analysing repeated-measures dataset with and without missing values, a mixed-effects model with random intercepts and slopes will be used to reveal significant differences in the outcome measures between the two groups over three time points (baseline, post day 1, and post day 30). Statistical significance will be based on *p* value threshold of 0.05. Any post hoc comparisons will be performed following the main analysis using Tukey’s tests. Cohen’s *d* will be employed to estimate the effect size of the change scores for this study. Questionnaire results will be reported via descriptive statistics (frequency analysis).

All results will be presented with 95% confidence intervals.

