## Methods/design

### Study design

An intensive robotic-based behavioural training for chronic stroke survivors, with emphases on retraining of proprioception and kinaesthesia, will be conducted. This is a two-arm RCT consisting of treatment and control groups. Participants are chronic stroke survivors from the local community in Singapore who will go through a series of training using their affected UL for 15 regular sessions. Each session will take place every alternate day, 3 days per week, for 5 weeks. On top of the training sessions, three behavioural and clinical assessments will be performed at baseline, post-day 1, and post-day 30, where the follow-up assessments will happen the following day and 30 days after the last training session respectively. All assessments will be administered by a therapist who is blinded to treatment allocation throughout the study. This therapist is different from the person who will be responsible for the routine intervention. Prior to the commencement of the study, the principal investigator will provide a half-day training session to the therapists involved. The process flow of this study is outlined in Fig 1, and the timeline of recruitment and enrolment processes, interventions, and study visits is summarised in the Standard Protocol Items: Recommendations for Interventional Trials (SPIRIT) diagram (Fig 2). This study was designed following the guidelines of the SPIRIT 2013 checklist (see Additional file 1).

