### Sample size

To estimate the sample size for this study, a Cohen’s *d* effect size of 0.5 was applied with a statistical power of 0.80 and an alpha level of 0.05. The resulting estimate is 28 participants in total based on the statistical power analysis programme G*Power (version 3.1.9.7). Approximately 36 participants will be screened and recruited, where 30 subjects will be estimated to complete the full study (with a conservative dropout rate of 20%).

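### Random slopes over three visits force each participant's change onto a straight line, although training ends before the second visit; depending on how time is coded, a fading gain can be missed or the post-day 1 standard error understated

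*Protocol article*

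**What the plan says.** The Statistical analysis section of the protocol article states that "a mixed-effects model with random intercepts and slopes will be used to reveal significant differences in the outcome measures between the two groups" and places this comparison "over three time points (baseline, post day 1, and post day 30"). It does not say whether time is numeric or a factor, or which term carries the test. It adds: "Any post hoc comparisons will be performed following the main analysis using" Tukey's tests. It also promises Cohen's d for change scores and 95% confidence intervals for all results.

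The Study design section fixes the timing. For training: "Each session will take place every alternate day, 3 days per week, for 5 weeks". For the later visits: "the follow-up assessments will happen the following day and 30 days after the last training session respectively". No study training takes place between post-day 1 and post-day 30.

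**The concern.** A random slope gives every participant a personal line through the three visits. The intervention works like a step: it acts between baseline and post-day 1 and is then withdrawn. A line cannot follow a rise that is then held or lost.

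What is at stake depends on the fixed part of the model, which is left open. If the group means are also modelled as lines, the group-by-time test asks whether two steady trends differ, and a gain that fades lies close to its null hypothesis. If the means are free at each visit, the estimates are right but the covariance is too rigid, so intervals and post hoc tests at post-day 1 can look more precise than they are. The Introduction says the results should inform a decision on larger multi-centre studies, so either error would matter.

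**Working it through.** **Inputs.** Three visits (Statistical analysis). Five weeks of training, then visits 1 and 30 days later (Study design): 5 × 7 = 35, so roughly days 0, 36 and 65. Thirty completers (Sample size: "where 30 subjects will be estimated to complete the full study") with equal allocation (Participants), so 15 per arm. The article gives no variances, correlations or time coding; those below are assumptions.

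**1. The plan's own sample size.** The stated inputs are "effect size of 0.5 was applied with a statistical power of 0.80 and an alpha level of 0.05", and "The resulting estimate is 28 participants in total". A group-by-time interaction in a repeated-measures ANOVA reproduces this, with f = d/2 = 0.25, 2 groups, m = 3 measurements, and correlation ρ = 0.5 and sphericity assumed:

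- λ = f² · N · m / (1 − ρ) = 0.0625 × 28 × 3 / 0.5 = 10.5, with 2 and 52 df: power 0.812.
- At N = 26, λ = 9.75: power 0.778. So N = 28.

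A one-sided paired t test gives 27, so the match is likely but not certain. If it is right, the calculation treated time as three levels.

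**2. What a random slope can mean here.** With one value per visit the within-participant covariance has 3 variances + 3 covariances = 6 free terms. Visit-level random effects need 6 parameters plus a residual, 7 in all, which is one too many. A linear random slope needs 2 variances + 1 covariance + 1 residual = 4. Only the linear version is practicable.

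**3. Reading A: time linear in the fixed part too.** Let the group difference be 0 at baseline, 1 at post-day 1 and r at post-day 30. The deviations of days 0, 36 and 65 from their mean are −33.67, 2.33 and 31.33, with sum of squares 2120.67. The least-squares slope over 65 days is 65 × (2.33 + 31.33 r) / 2120.67:

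- held (r = 1): 1.03
- half lost (r = 0.5): 0.55
- all lost (r = 0): 0.07

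Two sets of simulations with 15 per arm give this power:

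| Gain by post-day 30 | Set 1, linear | Set 1, categorical | Set 2, linear | Set 2, categorical |
|---|---|---|---|---|
| Held | 75-79% | 79-82% | 66-69% | 75% |
| Half lost | about 24% | 80-84% | 12-17% | 65% |
| All lost | 1-2% | 79-83% | 1% | 80% |

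Set 1: effect 1.06 SD of the change score, residual variance 0.3, SD of individual gain 0 to 1.0; the comparator is the unrestricted post-day 1 contrast. Set 2: effect 1 SD, correlation 0.5 throughout; the comparator is the joint 2-df test with visit as a factor. In set 2 the slope's standard error was not too small under this reading.

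**4. Reading B: visit a factor, random slope linear.** With complete data the post-day 1 contrast is the difference in mean change, with variance (2/15) × Var(change). Code the visits 0, 1, 2. With slope variance s² and residual variance v, the model gives Var(change) = s² + 2v in both intervals. If participants instead make a step of variance g that is held, with residual variance e, the true values are g + 2e in the first interval and 2e in the second. The large-sample fit takes their average, g/2 + 2e (checked numerically). Hence SE ratio = √[(g/2 + 2e) / (g + 2e)].

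| Assumed covariance | Ratio by formula | Simulated ratio | Simulated type I error, post-day 1 |
|---|---|---|---|
| Compound symmetry (g = 0) | 1.00 | 1.02 | 3.8% |
| g = 0.5, e = 0.3 | √(0.85/1.10) = 0.88 | 0.91 | 6.2% |
| Correlations 0.4/0.4/0.8 | √(0.80/1.20) = 0.82 | 0.84 | 7.8% |
| g = 1, e = 0.1 | √(0.70/1.20) = 0.76 | 0.81 | 9.5% |

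In the third row the two true change variances are 2(1 − 0.4) = 1.2 and 2(1 − 0.8) = 0.4, with average 0.8. Further runs with a held step gain gave type I error of about 7-11% and ratios of 0.78-0.90, while an unrestricted contrast stayed at 3-6%. The joint 2-df group-by-visit test stayed at about 4.5-6% in the runs tabulated here. Monte Carlo error is about 1 point near 5% and 2 points near 70%.

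**The case against.** The strongest reply is that the article never puts a straight line on the group means. A random slope describes variation between people and does not fix how time enters the fixed part. Tukey's tests compare factor levels, and the sample size matches a three-level interaction. This stands. A reader might infer that the plan tests a steady trend and will miss the training effect; the text does not support that, and reading A is the less likely one.

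Second, the robotic tests have 20 repetitions in the motor test and two blocks of 20 in the kinaesthetic test at each visit. If repetitions were modelled singly, visit-level random effects could be identified. This also stands, but the article does not say it will be done, and it would not help single-score scales such as the FMA-UE, which fall under the same model.

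Third, Cohen's d on change scores would show a day-1 gain whichever model is fitted. That protects the effect-size estimate under reading A, but not the significance test, nor the post-day 1 contrasts and intervals under reading B.

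Fourth, time coding and covariance details are commonly left to an analysis plan that is not shown. That excuses silence on coding. It does not excuse the random slope itself, which is stated and suits the design poorly.

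**Conclusion.** The concern holds in conditional form. What is firm is that, with one score per visit, the named random slope forces individual deviations onto a line that the training schedule does not imply. The two harms belong to different readings and do not add up.

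- Reading A: a serious loss of power, but only if the gain fades. The article does not predict fading.
- Reading B: a post-day 1 standard error about 10-20% too small and type I error of about 6-11%, but only if participants differ in a step-like gain. There is no problem under compound symmetry, and the joint test stays near 5%.

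A reader might infer error rates well above this. One set of runs with gain SD 1.0 and residual variance 0.1 reached 11-15%, but the last row of the second table, with the same gain and residual variances, gave 9.5%. The article supplies no variance component that would support the higher figure. Nor does it make post-day 1 the sole treatment effect: Primary outcome measures lists both follow-ups equally. The change is worth making, because a better-suited model is available at almost no cost.

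**What to change.** In Statistical analysis, replace the random intercepts-and-slopes model for the three-visit comparison with, for example:

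*Each outcome will be analysed with a repeated-measures mixed model with group, visit as a categorical factor and group-by-visit, and an unstructured within-participant covariance (REML; Satterthwaite or Kenward-Roger degrees of freedom). Between-group differences in change from baseline will be reported with 95% confidence intervals at both post-day 1 and post-day 30.*

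If individual repetitions of the robotic tests are to be modelled, say so and use visit-level rather than linear random effects.

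The model can be fitted in the SPSS already planned and needs no new data or participants. It keeps the handling of missing values for which a mixed model was chosen. The cost is two more covariance parameters (6 instead of 4) and a slightly wider post-day 1 interval.

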### Primary outcome measures

Two robotic-based tests will generate behavioural performance indices as the primary outcome measures of participants’ affected UL before (baseline) and after training (post-day 1 and post-day 30).

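### Cohen's d is based on raw change scores and the three-visit model states no baseline adjustment, so precision is given up in a pilot meant to estimate effect size

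*Protocol article*

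**What the plan says.** The Primary outcome measures section collects the robotic indices "before (baseline) and after training (post-day 1 and post-day 30"; the Secondary outcome measures section gives the clinical scales the same schedule. Every outcome therefore has a baseline value.

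The Statistical analysis section states that a mixed-effects model, with both intercepts and slopes random, "will be used to reveal significant differences in the outcome measures between the two groups over three time points", and it counts baseline among them: "over three time points (baseline, post day 1, and post day 30"). Cohen's d "will be employed to estimate the effect size of the change scores for this study". No baseline covariate and no constraint to a common baseline mean is mentioned. The fixed effects, the coding of time and the contrast that defines the treatment effect are not written out.

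The Sample size section says a Cohen's d "effect size of 0.5 was applied with a statistical power of 0.80 and an alpha level of 0.05", that "The resulting estimate is 28 participants in total based on the statistical power analysis programme G*Power", and that "30 subjects will be estimated to complete the full study". The Participants section gives equal allocation, hence about 15 per arm. The Introduction names effect-size estimation for later multi-centre work as one of the study's two purposes.

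**The concern.** A difference between arms in raw change subtracts the whole baseline value, although follow-up is only partly predicted by baseline. When the baseline-to-follow-up correlation is below 1, the subtraction over-corrects and adds noise. Adjusting for baseline removes only the predictable part, and in large samples is never less precise.

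This matters more than usual here. The arms are small, so chance baseline differences can be sizeable, and the effect size is itself a main product of the pilot. A noisier d is a poorer basis for planning the next trial, and the values needed to sharpen it are already being collected.

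**Working it through.** **Inputs.** From the protocol article: three time points including baseline; d on change scores; d = 0.5, power 0.80, alpha 0.05, total 28; 30 completers, so 15 per arm. Assumed, because the article does not give them: the baseline-to-follow-up correlation ρ, equal outcome variance σ² at baseline and follow-up, and a two-sided test.

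**Step 1: reproduce the plan's 28.** Take a repeated-measures ANOVA (within or within-between interaction) with f = d/2 = 0.25, 2 groups, m = 3 measurements, sphericity and ρ = 0.5:

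λ = f²·N·m/(1−ρ) = 0.0625 × 28 × 3 / 0.5 = 10.5, on 2 and (28−2) × 2 = 52 df.

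Power is 0.812; N = 26 gives 0.778. So 28 is consistent with baseline counted as one of three outcome measurements. This is not proof, since two measurements with ρ = 0.6 also give 28. A two-sided two-sample t-test at d = 0.5 would need 64 per arm, so that was not the source.

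**Step 2: what the three-visit model estimates.** Assume a group term, categorical time, group-by-time and complete data. Generalised least squares under a random-intercept covariance (intercept variance 1, residual variance 1, so ρ = 0.5 and total variance 2), with 15 per arm, gives for the post-day 1 contrast:

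- arm means free at every visit: variance 0.2667
- plain change score: (2/15) × (2 + 2 − 2×1) = 0.2667, identical
- arms constrained to a common baseline mean: 0.2000, which is 25% lower

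The first two also agree when a random slope is added (for example 0.2733 for both at ρ of about 0.49, against 0.2067 with the constraint).

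**Step 3: size of the loss.** Per observation, Var(change) = 2(1−ρ)σ² and Var(baseline-adjusted) = (1−ρ²)σ². The ratio is (1+ρ)/2, so the large-sample reduction is (1−ρ)/2. Estimating the baseline slope multiplies the adjusted variance by (N−3)/(N−4) = 27/26 = 1.038 at N = 30. The net reduction is 1 − 1.038 × (1+ρ)/2.

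| Assumed ρ | Ratio (1+ρ)/2 | Large-sample reduction | Net reduction, N = 30 |
|---|---|---|---|
| 0.3 | 0.65 | 35% | 32.5% |
| 0.5 | 0.75 | 25% | 22% |
| 0.7 | 0.85 | 15% | 12% |
| 0.8 | 0.90 | 10% | 6.5% |
| 0.9 | 0.95 | 5% | 1.3% |
| 0.95 | 0.975 | 2.5% | about −1% |

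A simulation with 15 per arm and 20,000 runs gave reductions of 34%, 23% and 7% at ρ = 0.3, 0.5 and 0.8, in line with the last column.

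**Step 4: what it means at 15 per arm.** At ρ = 0.5 the SD of change equals the outcome SD, so the difference detectable with 80% power is 1.06 SD. With adjustment it is 1.06 × √0.75 = 0.92 SD in the large-sample form, and 1.06 × √(0.75 × 1.038) = 0.94 SD after the slope cost. For a true 0.5 SD difference at one follow-up visit, power (change score against adjusted) is 20% against 27% at ρ = 0.3, 26% against 32% at 0.5, and 55% against 58% at 0.8.

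**Step 5: chance imbalance.** The SD of the baseline difference between arms is √(2/15) = 0.37 SD. At ρ = 0.5, an imbalance of that size shifts the change-score contrast by (1−0.5) × 0.37 = 0.18 SD, over a third of the planned d of 0.5. Adjustment removes this shift.

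**The case against.** The strongest objection is that the article names only a model class, the groups and the visits. The fixed effects could be settled in an analysis plan that is not shown, and a constrained longitudinal model would fit the published sentence as it stands. This is right as far as the model goes. The change-score equivalence in step 2 is an inference that needs a group term, categorical time and complete data; with linear time the contrast would be a slope difference. It does not reach Cohen's d, which the article places on change scores whatever model is fitted.

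It can also be said that ρ may be high: the Discussion describes chronic survivors as medically more stable, and each primary test block has 20 repetitions. That cannot be excluded, and near 0.9 the gain almost disappears.

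A reader might infer more than the article supports:

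- **That the effect estimate is biased.** Over randomisation the change-score contrast is unbiased. Imbalance shifts it in a given sample, and that is part of its variance.
- **That having baseline among the responses is the defect.** The constrained model keeps it there and is as efficient as covariate adjustment in large samples.
- **That the group-by-time test spends a degree of freedom on the baseline comparison.** With two groups and three visits, both interaction degrees of freedom are differences in change. The baseline difference would enter through the group main effect, which, if tested, would average in a pre-treatment visit.
- **That the gain is a known figure at no cost.** It depends on an assumed ρ, and the covariate slope has a price at this sample size.

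**Conclusion.** The point holds as a loss of precision. The reported d is unadjusted for baseline by the article's own wording. The model contrast is equivalent to a change score if the usual group-by-time specification is meant. At 30 completers the net variance reduction available is about 6.5% to 32% for assumed ρ between 0.8 and 0.3, falling to about 1% at 0.9 and to nil or slightly below at 0.95.

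At ρ = 0.5, the value that reproduces the plan's 28 with three measurements, the net 22% is worth about 28% more participants (1/0.779 = 1.28). Power for a 0.5 SD difference stays low either way, so adjustment does not rescue the sample size. It does sharpen the estimate that the pilot is meant to deliver, and it should be made before analysis.

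**What to change.** In the Statistical analysis section, state the fixed effects and the contrast of interest, using one of two forms:

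1. post-day 1 and post-day 30 as responses, with the baseline value and its interaction with time as covariates; or
2. all three time points as responses, with both arms constrained to a common baseline mean.

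Report the adjusted between-group difference at each follow-up visit with its 95% confidence interval, and base Cohen's d on that difference. Change-score d can be shown beside it if wanted for comparison with other studies.

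The cost is a few lines of wording and no new data. With the covariate model it is also one degree of freedom, about 4% of variance at 30 completers, which the net figures above already include.

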### Data management

The study has been approved by the Institutional Review Board (IRB) of the Nanyang Technological University, Singapore (IRB-2019-10-022). As part of the screening process, basic demographic information (e.g., age, gender, and ethnicity) and health information (e.g., handedness, side and type of stroke) will be recorded. Data collected will be de-identified using unique study code numbers. To maintain the privacy of the participants, any report of individual data will only consist of performance measures without any name, address, or identifying information which complies with the university IRB guidelines. All patient-related information and data generated by the robotic system will be maintained on a secure server owned by the university. Data monitoring will comply with the university policy, guidelines, and data management plan (DMP) approved for the study. At the completion of the study, the results will be submitted for publication in a peer-reviewed journal and presented at national and international conferences.

